### Study procedures

2.4

This study consists of four main parts, a questionnaire, clinical, imaging, and immunological part. A total of 20 patients will participate in all study parts while an additional 20 subjects will only participate in the questionnaire, clinical and imaging studies. Furthermore, the questionnaire study is open to all patients meeting the inclusion criteria, without participation in the other study parts. The study design is summarized in Figure 1.

**Figure 1 F1:**
[figure not shown]
A summary of the study design.

#### Part 1: Questionnaire studies

2.4.1

Validated questionnaires will be used to asses disease impact including physical activity (International Physical Activity Questionnaire (IPAQ)),^[18,19]^ functional impairment (Sickness Impact Profile (SIP)),^[20,21]^ pain (McGill's Pain Questionnaire (MPQ)),^[22,23]^ perceived fatigue (Checklist Individual Strength (CIS)),^[24,25]^ quality of life (RAND-36),^[26,27]^ mental health (Hospital Anxiety and Depression Scale (HADS)),^[28,29]^ lower urinary tract symptoms (International Prostate Symptom Score (IPSS)),^[30,31]^ increased bleeding tendency (Molecular and Clinical Markers for the Diagnosis and Management of Type 1 von Willebrand disease (MCMDM-1VWD Bleeding Questionnaire)),^[32]^ and worries about the occurrence of a MH or ERM episode (modified version of the Cancer Worry Scale (CWS)).^[33]^ Furthermore, purpose-designed questionnaires focusing on neuromuscular, cardiac and respiratory symptoms will be used as tools to explore topics of interest for future research.

Subjects included in this part of the study will fill out digital questionnaires at three-time points; upon recruitment (t = 0), at 6 months (t = 1) and at 12 months (t = 2). A detailed timeline of the study design of the questionnaire study is given in Table 1.

**Table 1 T1:** Summary of the study design of the questionnaire study.

Questionnaire	Time point 1 (inclusion)	Time point 2 (6 months)	Time point 3 (12 months)
IPAQ ^[18,19]^	x	X	x
SIP ^[20,21]^	x	X	x
MPQ ^[22,23]^	x	X	x
CIS ^[24,25]^	x	X	x
RAND-36 ^[26,27]^	x	X	x
HADS ^[28,29]^	x	x	x
IPSS ^[30,31]^	x		
MCMDM-1VWD Bleeding Questionnaire ^[32]^	x		
Modified CWS ^[33]^	x	x	x
Neuromuscular symptoms questionnaire	x		
Cardiovascular symptoms questionnaire		x	
Respiratory symptoms questionnaire			x

IPAQ = International Physical Activity Questionnaire, SIP = Sickness Impact Profile, MPQ = McGill's Pain Questionnaire, CIS = Checklist Individual Strength, HADS = Hospital Anxiety and Depression Scale IPSS = International Prostate Symptom Score, MCMDM-1 VWD = Molecular and Clinical Markers for the Diagnosis and Management of Type 1 von Willebrand disease, CWS = Cancer Worry Scale.

#### Part 2: Clinical studies

2.4.2

General information on the medical history, current medication, body weight and height and results from previous investigations (e.g. muscle biopsies, electromyography) will be collected from the electronic health records.

The degree and extent of muscle weakness will be measured using Medical Research Council (MRC)-scores and quantitative myometry using a fixed myometry testing. Hypermobility will be rated using the Bulbena^[34]^ and Beighton score.^[35]^ Respiratory muscle weakness will be tested using spirometry in sitting and supine position (vital capacity, forced vital capacity, forced expiratory volume in the first second). In addition, a timed up and go test,^[36]^ 30 seconds sit to stand test^[37]^ and a six-minute walking test will be performed.^[38]^ Furthermore, resting CK levels will be measured during the visit at the outpatient clinic.

#### Part 3: Imaging studies

2.4.3

The imaging study consists of two parts, a muscle ultrasound and a muscle MRI. Previous studies in facioscapulohumeral dystrophy have shown that these techniques are complementary, since ultrasound is most sensitive in early stage of the disease while MRI sensitivity increases in later disease stages.^[39]^

##### Ultrasound

2.4.3.1

A quantitative and qualitative muscle ultrasound examination will be performed using an Esaote MylabTwice ultrasound scanner (Esaote SpA, Genoa, Italy) with a 3–13 MHz broadband linear transducer. The protocol will include a bilateral ultrasound of the musculus trapezius, deltoideus, biceps brachii, thoracic and lumbar erector spinae, iliopsoas, proximal vastus lateralis, biceps femoris and gastrocnemius (medial head). The ultrasound protocol was previously reported elsewhere.^[40]^ Briefly, a strict preset for system settings will be used to ensure reproducibility. Three consecutive measurements will be performed, and results will be averaged offline. For every muscle, a region of interest is drawn manually to calculate the mean echogenicity using the histogram function of a custom image analysis package. Using age, sex and weight corrected reference values, Z-scores (the number of standard deviations from the mean) will be calculated for each muscle. Z-scores below 2 (i.e. below the population 95th percentile) are considered normal.

A semi-quantitative assessment of the images will be performed using the Heckmatt rating scale which ranges from one (normal echo-intensity) to four (severely increased echo-intensity with absent bone reflection) by an experienced neuromuscular ultra-sonographer.^[41]^

##### MRI

2.4.3.2

A whole-body MRI will be performed using a 1,5 Tesla MR system (Avanto Fit, Siemens, Erlangen, Germany). Volumetric Interpolated Breath-hold Examination (VIBE) 2-point DIXON (proton density weighted) and Short-TI Inversion Recovery (STIR) sequences will be acquired. STIR images will be used as an indicator for edema and/or inflammation. The VIBE 2-point DIXON images will be used to evaluate muscle volume and presence of fatty infiltration.

#### Part 4: Immunology

2.4.4

Immunological investigations will include a set of laboratory studies using blood samples from a subset of 20 *RYR1* patients and 40 age and sex matched healthy controls. Healthy controls will be recruited amongst volunteers from the staff members of the Radboud University Medical Centre and the Canisius Wilhelmina Hospital.

Peripheral mononuclear blood cells (PBMC) will be isolated from EDTA blood of *RYR1* patients and healthy controls. PBMCs will be stimulated for 24 hours with the Toll-like receptor (TLR) ligands *Escherichia coli* lipopolysaccharide (LPS) and heat-killed Candida in the presence of RyR1 agonists 4-CmC and caffeine and/or the RyR1 antagonist dantrolene. Cytokine levels (IL-1β, IL-6 and TNF-α) in the supernatant of the ERM/MHS subjects will be compared to healthy controls.^[9,12,13]^ Additionally, circulating cytokines (IL-1β, IL-6) will be measured in all participating patients.^[9]^

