### Statistical analysis

2.5

Continuous variables will be summarized by their mean and standard deviation or median and interquartile ranges depending on its distribution. Categorical data, including ordinal data, will be summarized in terms of percentages. Results from the questionnaire studies and cytokine production from *RYR1* patients will be compared to normal values and (if applicable) healthy controls using the students *t*-test.

Due to the explorative nature of this study we did not perform a power calculation. For the clinical and imaging studies, 40 subjects will be included since previous studies and case series with similar sample size showed a substantial clinical and histopathological overlap in patients with congenital myopathies and ERM or MH susceptibility.^[3,5,6]^ For the immunological studies, 20 MHS/ERM patients and 40 healthy controls will be included as previous studies in animal models showed an immunological gain-of-function in MHS mice in a lower number of subjects.^[12,13]^ The number of healthy controls is twice the number of MHS/ERM subjects as more variance is expected in the healthy controls than in the MHS/ERM subjects.

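### The between-group t-test on stimulated cytokine levels does not isolate the RyR1-dependent response; the group-by-condition contrast should be named as the RyR1-specific result

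*Protocol article*

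**What the plan says.** Section 2.4.4 (Part 4: Immunology) stimulates cells from patients and healthy controls for 24 hours with LPS and heat-killed Candida "in the presence of RyR1 agonists 4-CmC and caffeine and/or the RyR1 antagonist dantrolene". The comparison it gives for the supernatants is: "Cytokine levels (IL-1β, IL-6 and TNF-α) in the supernatant of the ERM/MHS subjects will be compared to healthy controls". The groups are "20 *RYR1* patients and 40 age and sex matched healthy controls", and the controls are volunteers from hospital staff. The type of matching, individual or by frequency, is not stated.

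Section 2.5 (Statistical analysis) names the test: "cytokine production from *RYR1* patients will be compared to normal values and (if applicable) healthy controls", by Student's t-test. It does not say paired or unpaired. No contrast between wells with and without a RyR1 modulator is stated, and neither is a significance level.

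Three other places show what the modulator wells are for. The Introduction reports that B-cells from MH-susceptible carriers were more sensitive to 4-CmC and made more IL-1β and IL-6 after 4-CmC and caffeine. Section 2.2 makes the role of the immune system as a modifying factor a secondary objective. The Discussion expects the results to clarify what RyR1 does in the immune system.

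**The concern.** Greater sensitivity to an agonist is a change from the state without the agonist. If each donor's cells are cultured under several conditions, the RyR1-dependent response is the within-donor change from ligand alone to ligand plus modulator. The variant-related question is whether that change differs between patients and controls. The stated comparison looks at the level in each group instead.

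Patients come from MH and ERM cohorts and controls from hospital staff. The two groups could differ in general TLR responsiveness for reasons unrelated to RyR1. Such a difference would carry through to the 4-CmC, caffeine and dantrolene wells, where a significant t-test invites a RyR1 interpretation. At stake is the attribution of the finding under a stated secondary objective.

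**Working it through.** **Inputs.** From the protocol: 20 patients and 40 controls, Student's t-test, cytokine levels. Assumed, because the protocol gives no values: two-sided 0.05, normal outcomes with equal SD (set to 1), within-donor correlation rho between two wells, and effects of 0.75 SD. No power calculation was done, so there is no planned figure to reproduce.

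**1. What each test targets.** Let b be the patient-minus-control difference with ligand alone, and i the extra difference that appears when the agonist is added.
- Level test in the agonist well: expected difference b + i.
- Test of the within-donor change: expected difference (b + i) − b = i.

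The level test cannot separate b from i, whatever the sample size.

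**2. Size of the effect on conclusions.** Simulated rejection rates, 20,000 runs each:

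| b (SD) | i (SD) | Level test, agonist well | Change test, rho 0.5 | Change test, rho 0.8 |
|---|---|---|---|---|
| 0 | 0 | 5% | 5% | 5% |
| 0.75 | 0 | 77% | 5% | 5% |
| −0.75 | 0.75 | 5% | 77% | 99% |
| 0 | 0.75 | 77% | 77% | 99% |

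Row 2 is the misattribution: no difference in agonist response, yet the level test usually rejects. Row 3 is the reverse: a real difference in response is hidden by an opposite baseline difference. Row 4 shows that with equal baselines the level test does detect the response.

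**3. Precision of the contrast.** The SD of a change is √(2(1 − rho)) times the SD of a level, so the SE ratio of change to level is:
- rho 0: √2 = 1.41
- rho 0.3: √1.4 = 1.18
- rho 0.5: √1 = 1.00
- rho 0.7: √0.6 = 0.77
- rho 0.8: √0.4 = 0.63

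The difference in level detectable with 80% power is (1.960 + 0.842) × √(1/20 + 1/40) = 2.802 × 0.274 = 0.77 SD. For the change it is 0.77 × 1.18 = 0.91 SD at rho 0.3 and 0.77 × 0.77 = 0.59 SD at rho 0.7.

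**4. Matching, only if controls are individually matched 1:2.** With within-set correlation r, the variance of a patient minus the mean of the two controls is 1.5σ²(1 − r), against 1.5σ² in an unpaired test. The actual type I error of the unpaired test is then 2(1 − Φ(1.96/√(1 − r))): 0.039 at r = 0.1, 0.028 at 0.2 and 0.019 at 0.3. Power at 0.75 SD is 0.81 unpaired against 0.87 matched at r = 0.2, and 0.82 against 0.91 at r = 0.3. The unpaired test is conservative and loses power; it is not biased.

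**The case against.** The strongest reply is that comparing patients and controls in the presence of 4-CmC or caffeine already bears on RyR1, that the Introduction cites earlier work in that same form, and that Section 2.2 names no RyR1-specific estimand. This stands in part. A reader might infer that the plan fails to test the RyR1 response at all; row 4 of the table shows otherwise. What the level test lacks is specificity.

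A reader might also infer that the plan throws away the age and sex matching. The document does not support that. An unpaired test is the natural reading of 20 against 40, but the protocol does not say it. Under frequency matching there are no sets to analyse, and the design still balances age and sex.

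The article is condensed and the study is called exploratory, so model details may be in a document not shown. That excuses missing detail. It does not remove the point, because the article states a comparison and a test, and these do not isolate the modulator response.

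Two further limits stand. A change on the log scale cancels only donor effects common to all wells on that scale; a patient-staff difference in responsiveness to the modulator for other reasons would remain. The SE ratios in step 3 compare two different quantities, so they should not be converted into a saving in donors.

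**Conclusion.** The point holds in this form: the stated t-test on cytokine levels does not isolate the RyR1-dependent response, and a general difference in TLR responsiveness could be misread as a RyR1 effect. Under an assumed general difference of 0.75 SD and no difference in agonist response, rejection is about 77% for the level test against about 5% for the change.

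That the two tests target b + i and i needs no assumption about effect sizes. The percentages rest on the assumed effects, the 0.05 level, and normal outcomes with equal SDs, whereas Section 2.5 expects more variance in controls. The precision of the contrast depends on an unknown within-donor correlation and can be better or worse than that of the level comparison. The matching is a secondary matter of efficiency, and only if sets were individually formed.

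**What to change.** For each ligand and cytokine, analyse log concentrations in a mixed model with group, condition, group × condition, age and sex, and a donor random intercept. Report the group × condition contrasts (4-CmC, caffeine and dantrolene, each against ligand without modulator) as the RyR1-specific result. Keep group differences in level alongside as supporting results. State whether "40 age and sex matched healthy controls" means individual or frequency matching, and add a matched-set effect only if it is individual.

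**Cost.** A change of analysis wording and modest extra analysis, with no new participants. It requires a ligand-without-modulator well for every donor. The article does not describe one, so the sponsor should confirm it; without it these contrasts cannot be computed. If the within-donor correlation is below 0.5, the contrast is less precise than the level comparison (SE about 1.18 times at 0.3, against 0.77 times at 0.7), which is a further reason to report both.

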### Statistical analysis

2.5

Continuous variables will be summarized by their mean and standard deviation or median and interquartile ranges depending on its distribution. Categorical data, including ordinal data, will be summarized in terms of percentages. Results from the questionnaire studies and cytokine production from *RYR1* patients will be compared to normal values and (if applicable) healthy controls using the students *t*-test.

Due to the explorative nature of this study we did not perform a power calculation. For the clinical and imaging studies, 40 subjects will be included since previous studies and case series with similar sample size showed a substantial clinical and histopathological overlap in patients with congenital myopathies and ERM or MH susceptibility.^[3,5,6]^ For the immunological studies, 20 MHS/ERM patients and 40 healthy controls will be included as previous studies in animal models showed an immunological gain-of-function in MHS mice in a lower number of subjects.^[12,13]^ The number of healthy controls is twice the number of MHS/ERM subjects as more variance is expected in the healthy controls than in the MHS/ERM subjects.

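### The cytokine comparison is planned with Student's t-test at 20 versus 40, yet the 1:2 ratio is justified by unequal variances; under that expectation the pooled test is conservative and loses power

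*Protocol article*

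**What the plan says.** Section 2.5 (Statistical analysis) states that questionnaire results and cytokine production "will be compared to normal values and (if applicable) healthy controls using the students *t*-test". It names no unequal-variance version of the test. Section 2.4.4 (Part 4: Immunology) makes clear that the patient-control contrast concerns IL-1β, IL-6 and TNF-α, whose levels "in the supernatant of the ERM/MHS subjects will be compared to healthy controls".

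For the size of this part, section 2.5 says that "20 MHS/ERM patients and 40 healthy controls will be included" and explains the ratio by the larger variance expected in the controls ("as more variance is expected in the healthy controls than in the MHS/ERM subjects"). It gives no SD, variance ratio or significance level, and it says: "Due to the explorative nature of this study we did not perform a power calculation".

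**The concern.** Student's t-test in its usual form estimates one common variance from both groups. With equal group sizes, unequal variances do little harm. With unequal sizes the pooled estimate is dominated by the larger group, and the standard error of the difference is biased in a direction that depends on which group varies more.

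The plan expects the larger group, the controls, to be the more variable. The standard error is then overstated, so real differences are missed more often than they need be. If that expectation proved wrong and patients varied more, the bias would reverse and false positives would increase. At stake is the sensitivity of the immunological comparison, the second of two secondary objectives in section 2.2, in a study with only 20 patients in this part.

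**Working it through.** **Inputs from the plan.** n₁ = 20 patients; n₂ = 40 controls; Student's t-test; variance expected to be larger in controls (all section 2.5). The sample size has no power calculation behind it, so there is no planned figure to reproduce.

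**Assumptions.** Normal data; two-sided 5% level; patient SD σ₁ = 1; control SD σ₂ = r, with r varied because the plan gives no value.

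**Standard error.**

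- True variance of the difference in means: σ₁²/n₁ + σ₂²/n₂.
- Expected pooled estimate: [(n₁−1)σ₁² + (n₂−1)σ₂²]/(n₁+n₂−2) × (1/n₁ + 1/n₂).

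At r = 2:

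- True: 1/20 + 4/40 = 0.150.
- Pooled: (19×1 + 39×4)/58 × (1/20 + 1/40) = (175/58) × 0.075 = 0.226.
- Ratio of standard errors: √(0.226/0.150) = 1.23, so the standard error is 23% too large.

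At r = 1.5:

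- True: 1/20 + 2.25/40 = 0.10625.
- Pooled: (19 + 39×2.25)/58 × 0.075 = 0.138.
- Ratio: √(0.138/0.10625) = 1.14.

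**Type I error, coverage and power.** Simulation at 20 versus 40, with 400,000 replicates per scenario. For power, the true difference was set at (1.960 + 0.842) × true standard error, which is 80% power by the normal approximation. Coverage is that of a 95% interval for the difference built from the pooled standard error.

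| Control:patient SD ratio | SE, pooled/true | Type I error, pooled | Coverage, pooled | Power, pooled | Power, Welch |
|---|---|---|---|---|---|
| 1.0 | 1.00 | 5.0% | 95.0% | 78.6% | 77.8% |
| 1.1 | 1.03 | 4.3% | 95.7% | 76.7% | 78.1% |
| 1.25 | 1.08 | 3.5% | 96.5% | 73.9% | 78.2% |
| 1.5 | 1.14 | 2.6% | 97.4% | 69.8% | 78.5% |
| 2.0 | 1.23 | 1.8% | 98.3% | 63.6% | 78.6% |
| 3.0 | 1.32 | 1.1% | 98.9% | 56.7% | 78.5% |

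For scale, 1:2 is the most efficient split of a fixed total of 60 when the SD ratio is 2. The plan does not claim that ratio.

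**Opposite direction (patients more variable).** At r = 0.67 the pooled test has type I error 8.6% and coverage 91.4%; at r = 0.5, 11.1% and 88.9%.

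**Two cross-checks.** Welch's test stays between 4.95% and 5.06% type I error at every ratio tried (0.5 to 3). With 30 versus 30, the pooled test stays between 5.0% and 5.3% over the same ratios. The problem therefore comes from unequal variances combined with unequal group sizes.

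**The case against.** **The variant is not stated.** The article says only Student's t-test, and it condenses a fuller plan that might specify Welch's form. This stands as a caveat: pooling is inferred from the usual meaning of the name. It does not remove the point, because the article itself names the test and, in the same section, states an expectation that the test's usual form contradicts. If Welch was intended, the same sentence settles it.

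**The plan's own scenario produces no excess of false positives.** This is correct. A reader might infer that the pooled test inflates false positives; that requires patients to be the more variable group, the opposite of what section 2.5 expects, and no figure in the article supports it. Patients do mix MH susceptibility with ERM and three variant classes (section 2.3.1), so the reverse cannot be excluded, but it is a possibility and not the planned case.

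**The extra controls are not wasted.** A reader might conclude that the test undoes the reason for recruiting 40 controls. It does not. For the same true difference at each ratio, the pooled test has power of about 59.6% with 20 versus 20 and 69.8% with 20 versus 40 at an SD ratio of 1.5. At a ratio of 2 the figures are about 56.3% and 63.5%. The gain is reduced, not lost.

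**The effect may be small.** This also stands. At a ratio of 1.1 the loss is 78.1 − 76.7 = 1.4 points of power, and the plan gives nothing from which to choose a ratio.

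**Conclusion.** The point holds as an inconsistency within section 2.5: the named test usually assumes equal variances, while the group sizes are justified by unequal ones. In the expected direction the consequence is a conservative test with less power than the same data could give. Over assumed SD ratios of 1.1 to 2, the loss against Welch's test runs from about 1.4 to 15 points (78.6 − 63.6 = 15.0 at a ratio of 2). These figures rest on normal data, an assumed two-sided 5% level and assumed ratios.

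It would go too far to say that the study's p-values and error bars are wrong throughout. The article specifies no error bars, confidence interval or significance level. The group SDs and interquartile ranges do not depend on pooling, and comparisons with fixed normal values are not affected by the 20 versus 40 imbalance. Only the standard error, p-value and any interval for the patient-control difference are touched.

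This should be fixed, but it is not critical: the study is exploratory, the immune question is a secondary objective, and the primary objective does not depend on this test.

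**What to change.** In section 2.5, state that patient-versus-control cytokine comparisons use Welch's unequal-variance t-test. Any confidence interval reported for the difference should come from the same method.

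The cost is one sentence. It needs no further data or participants, and if the variances turn out equal the power loss is 78.6 − 77.8 = 0.8 points under the assumptions above. The group sizes and the descriptive summaries can stay as they are. The documents give no cytokine distribution and do not say on which scale the larger variance is expected, so this point does not support prescribing a transformation.
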